## Abstract

**Background:**

Aged patients with coronary heart disease (CHD) have a high prevalence of co-morbidity associated with poor quality of life, high health care costs, and increased risk for adverse outcomes. These patients are often lacking an optimal home care which may result in subsequent readmissions. However, a specific case management programme for elderly patients with myocardial infarction (MI) is not yet available. The objective of this trial is to examine the effectiveness of a nurse-based case management in patients aged 65 years and older discharged after treatment of an acute MI in hospital. The programme is expected to influence patient readmission, mortality and quality of life, and thus to reduce health care costs compared with usual care. In this paper the study protocol is described.

**Methods/design:**

The KORINNA (Koronarinfarkt Nachbehandlung im Alter) study is designed as a single-center randomized two-armed parallel group trial. KORINNA is conducted in the framework of KORA (Cooperative Health Research in the Region of Augsburg). Patients assigned to the intervention group receive a nurse-based follow-up for one year including home visits and telephone calls. Key elements of the intervention are to detect problems or risks, to give advice regarding a broad range of aspects of disease management and to refer to the general practitioner, if necessary. The control group receives usual care. Twelve months after the index hospitalization all patients are re-assessed. The study has started in September 2008. According to sample size estimation a total number of 338 patients will be recruited. The primary endpoint of the study is time to first readmission to hospital or out of hospital death. Secondary endpoints are functional status, participation, quality of life, compliance, and cost-effectiveness of the intervention. For the economic evaluation cost data is retrospectively assessed by the patients. The incremental cost-effectiveness ratio (ICER) will be calculated.

**Discussion:**

The KORINNA study will contribute to the evidence regarding the effectiveness of case management programmes in aged people with MI. The results can be an important basis for clinicians, administrators and health policy makers to decide on the provision of high-quality care to older patients with CHD.

**Trial registration:**

ISRCTN02893746

## Background

### Coronary heart disease (CHD) in aging populations

The aging of the population and the increasing prevalence of chronic diseases imply great challenges to the health systems of developed countries. CHD is the leading cause of mortality and morbidity in the industrialized world. The treatment of acute myocardial infarction (MI) has improved dramatically over the last 10 to 20 years and nowadays, aged patients with an acute MI are receiving treatment that had been limited to mainly younger patients about a decade ago [1]. Subsequently, the number of survivors with MI will increase in the next decades.

Patients with CHD, in particular aged patients, have a high prevalence of co-morbidity associated with poor quality of life, physical disability, high health care costs, multiple medications, and increased risk for adverse outcomes. Common co-morbidities among patients with CHD are diabetes, chronic heart failure (CHF), chronic obstructive pulmonary disease (COPD), and depression [1-3]. CHD is the most common reported cause of chronic heart failure in all age-groups [4]. A number of studies also found that more aged than young patients develop CHF following an acute MI: 47% of those aged greater than 75 years versus 23% aged < 75 years [5]. In addition, diabetes is not only a co-morbidity of CHD, but is also an independent risk factor for the development of CHF particularly in the aged [6]. CHF is the most common cause of hospital admission in the aged [7], and more aged than younger patients with CHF are discharged to long-term care and this number is increasing [8]. Thus, as a rule, aged patients do not present with an isolated medical problem, but have multiple co-morbid diseases [9]. Consequently, these patients receive a number of medications [10].

Due to changes in the German health care system, in particular the establishment of the diagnosis related groups (DRG) system, older patients with complex health care needs are nowadays discharged earlier from hospital than a few years ago [11]. For many of these patients an optimal care at home is not guaranteed, resulting in subsequent readmissions or final admission to a nursing-home. Medication compliance and lack of medication-related knowledge are serious problems in aged patients, and in higher age-groups there is also often a lack of social support or knowledge to seek medical support promptly, when specific symptoms appear [12]. Thus, optimizing care for this population has a high priority.

Many hospital admissions among aged patients with CHD can be attributed to behavioural and social factors rather than to deteriorating cardiac function or an intercurrent cardiac event [13]. Thus, aged multimorbid patients at risk of poor outcomes might benefit from intensive home follow-up. A nurse-led home-based intervention program including patient education and counselling might improve medication compliance, medication-related knowledge and thus processes of care, coronary risk factor profiles, functional status, and quality of life. As a consequence, this might reduce mortality. In addition, such a program is expected to reduce health care resource use in patients with CHD and consequently total health care expenditures.

### Case management programmes for patients with CHD

A number of intervention trials investigated whether a nurse-based case management may influence patient readmission and other outcomes in CHD [14,15]. In a meta-analysis investigating the effectiveness of secondary prevention programmes with and without exercise components 63 randomized trials were included [14]. Almost all included studies were conducted in patients with CHD younger than 70 years. It could be shown that secondary prevention programmes positively affect process of care, survival, and functional status or quality of life of patients with CHD independent of the applied programme.

In another review McAlister et al. examined whether case management programmes for patients with established CHD improve the process of care and reduce mortality [15]. In total 12 randomized trials also including mainly patients younger than 70 years could be identified by the investigators. It could be demonstrated that comprehensive case management programmes have a positive effect on processes of care in patients with CHD: there was a significant reduction in admissions to hospital and an improvement in quality of life. However, these randomized clinical trials failed to document any survival benefit or reduction in recurrent MI.

Although the results of both studies, the meta-analysis and the review, are promising, these findings can not be generalized to higher age-groups. Very few studies reported on case management programmes in people older than 65 years. The studies by Naylor et al [16,17] examined a nurse-centered discharge planning and home follow-up intervention in patients older than 65 years with a broad variation of diagnoses and interventions. Their study on older people with CHF (mean age 76 years) demonstrated that the intervention significantly increased the length of time between hospital discharge and readmission or death, reduced total number of rehospitalizations, and decreased healthcare costs [17].

Regarding cost-effectiveness of the case management programmes it is notable that only seven of the 63 trials included in the meta-analysis by Clark et al. [14] described the costs of the intervention. Two reported that their intervention was cost saving but only one has performed formal cost-effectiveness analyses. From the twelve studies included in the review by McAlister et al. [15], three described cost data and two reported that their intervention was cost saving, but none performed formal cost-effectiveness analyses. Based on the observed lack of formal economic evaluations in these studies and the conflicting results, the need to systematically integrate economic evaluations into such studies was highlighted by the authors [14,15].

Overall, the review of the literature showed that studies on case management programmes mostly included participants with CHD younger than 70 years [14] or included persons hospitalized with one of several common medical and surgical reasons [18,19]. So far, no intervention trial focused on a specific case management programme for the group of aged patients after MI. Case management focuses on delivering personalized services to patients to improve their care. Case management after hospital discharge could play a central role for the prevention of re-infarction or readmission for other reasons among aged patients with an acute MI.

### Objective of the study

The primary objective of the study is to assess whether a case management intervention by trained nurses can reduce time to first readmission or out-of-hospital death in aged patients with MI. Secondary objectives are the estimation of the cost-utility ratio of this case management intervention and to compare case management vs. routine care with respect to secondary out-comes such as functional capacity, participation, quality of life, and compliance with medication. For patients with specific comorbidity, additional outcome criteria will be compared between the two groups, e.g. adjustment of blood glucose values and hemoglobin-A_1c _in patients with type 2 diabetes, and maintenance of body weight in patients with CHF.

The aim of this paper is to describe the study protocol of the KORINNA (Koronarinfarkt-Nachbehandlung im Alter) study. Patient recruitment in the KORINNA study has started by September 2008. This detailed description of the study background and protocol is published as a reference for forthcoming papers on the study results.

## Methods/Design

### Study design

The study is designed as a single-centre randomized two-armed parallel group trial. The study is carried out within the framework of KORA (Cooperative Health Research in the Region of Augsburg). All patients receive a baseline assessment after giving their informed consent. The baseline assessment is carried out by the study physician and a study nurse. Those who are subsequently randomized to the intervention group receive the intervention starting with the initial session shortly before discharge (see Figure 1). All patients are contacted by phone after 3, 6, and 9 months in order to document a core set of relevant outcome measures. The duration of the intervention phase is one year. After one year a final investigation takes place in the hospital or at home.

**Figure 1 F1:**
[figure not shown]
**Study design**.

### Patient selection

#### Inclusion criteria

In the KORINNA study all patients of the age group 75 years and older with a first or recurrent MI during the planned recruitment period who are treated in the Augsburg Hospital should be included. The Augsburg Hospital is the largest hospital in the region of Augsburg - a city with 300,000 inhabitants in the south of Germany - offering a coronary care unit as well as coronary angiography and angioplasty facilities 24 hours a day. All myocardial infarctions according to ESC and ACC criteria will be included [20].

However, an unexpected low number of patients of the age group 75 years and older became apparent during the first year. As a consequence, the study protocol was modified and the minimum age of participants was set to 65 years. The recruitment phase needs to be expanded accordingly. This modification was discussed with the studies' Advisory Board.

#### Exclusion criteria

Patients who already live in institutionalized care are excluded. In addition, patients who already plan to move into institutional care or outside the study region within the next months are excluded as well. Furthermore, patients with severe comorbidity (e.g. terminal cancer) which makes rehospitalization within the next months necessary or is associated with a life expectancy of less than one year, and patients who are not able to communicate in German language are excluded. Finally, patients who are unable or unwilling to give written informed consent (e.g. patients with dementia) cannot be included in the study. The number of patients not included in the study as well as reasons for exclusion will be documented.

The study protocol and its amendment were approved by the Ethics Committee at the Bavarian Chamber of Physicians (Date of approval: 11.11.2008, Reference number: 08064). Furthermore, the study is conducted in accordance to German privacy law and in compliance with the Helsinki Declaration.

### Randomization

All patients meeting the inclusion criteria and giving informed consent are randomly assigned to the intervention or control group. The allocation ratio is 1:1. To ensure the concealment of the allocation, randomization is provided per telephone call to the biostatistical center at the Helmholtz Zentrum München, German Research Center for Environmental Health, where a randomization list is kept. A minimization procedure is used which tries to achieve balanced treatment groups with respect to gender, age (< 70 vs. 70-79 vs. 80+), and number of comorbidities (diabetes and CHF).

### Intervention

The intervention consists of a nurse-led individualized home-follow up programme with a duration of one year. The control group receives usual care. Patients can use or apply for all available services in the area.

#### Initial session before discharge

The intervention programme starts with an initial information session (approximate duration 1 hour) which takes place one or two days before hospital discharge (see Figure 1). In this session the patient is first of all provided with information about the disease and comorbidities, about medication and with behavioural recommendations (nutrition, physical activity, smoking etc.). Information is given orally and in written form (so-called "heart book"). If possible, close relatives of the patient may participate in the discharge session. A first home visit is arranged, if accepted by the patient, otherwise an appointment for a telephone call is made.

#### Home visits and telephone calls

Home visits (0 to 4) and telephone calls (at least every 3 months) are carried out according to patient need and patient risk level. At the first home visit the specific problems of the patient are identified and documented. An individual plan for each patient is set up. The risk level is assessed by the study nurse during the first home visit based on compliance, the social network, and the comorbidities. The higher the risk level the more contacts (telephone and home visits) are arranged by the study nurse. The activities are planned in agreement with the patient in order to improve compliance.

The first home visit is scheduled to take place 7 to 14 days after discharge. If the patient stays in a rehabilitation hospital immediately after discharge from the Augsburg hospital, the first home visit will be postponed accordingly. At the home visits patients are instructed how the prescribed drugs have to be taken and what would happen in the case of non-compliance with medication. Furthermore, to patients with diabetes advice is given regarding nutrition and physical activity, and patients with CHF are encouraged to regular weight control. During the visits, measurements of blood glucose, blood pressure, and weight are performed. The duration of the visit should be between 60 and 90 minutes. The key elements of both the home visits and the telephone calls are: to detect problems (e.g. regarding intake of medication) or risks, to give advice regarding a broad range of aspects of disease management (e.g. health behaviour) and to refer to the general practitioner, if necessary. The content and structure of home visits and telephone calls are comparable, and primarily differ regarding location and type of contact between the patient and nurse, and the possibility to measure blood glucose, blood pressure, and weight.

#### Training

In August 2008, a training of the three study nurses and the study physician was performed lasting several days. The following topics and diseases were intensively discussed with the study nurses: CHD, MI, angina pectoris, heart failure, treatment of MI, risk factors of cardiovascular diseases, action of particular drugs, diabetes mellitus, psychological factors and MI. Furthermore, the structure and the contents of the "Heart book" handed out to the patients in the intervention group at discharge were discussed.

Regarding the study implementation, both study physician and study nurses received a training on patient recruitment. The study physician was instructed on patient information and obtaining informed consent. Moreover, the procedure of the clinical examination and personal interview was trained.

Finally, study nurses were introduced in the performance of personal interviews in the hospital, of home visits, and of telephone interviews, the use of the intervention modules, the data extraction from patients' records, documentation, and data entry.

### Baseline and outcome assessments

The primary endpoint of readmission is measured as time between initial hospital discharge and first unplanned readmission to hospital (at least for 24 hours). Out of hospital death from any cause is counted as an event.

The instruments used to assess secondary outcomes are shown in Table 1. Baseline data on all recruited patients (intervention and control group) are collected at the index hospitalization, usually one or two days before the patient will be discharged. Data on sociodemographic and health status characteristics, functional status, participation, and psychosocial status are collected by the study physician and a trained study nurse. After discharge, standardized non-interventional telephone interviews with the patients in both groups are planned at 3, 6, and 9 and 12 months after index hospital discharge identifying patient's readmissions, acute care visits to physicians, clinics, and ambulatory departments. Data on quality of life is also collected during these interviews. In the intervention group additional telephone calls as well as home visits take place as part of the intervention. Additional information is documented on these opportunities in order to monitor process quality.

**Table 1 T1:** Outcome measures

Category	Instrument	Reported by	T_0_	T_3_	T_6_	T_9_	T_12_
Anamnesis	Baseline questionnaire	Physician	•				
Anamnesis	Geriatric Assessment [26]	Physician	•				
Quality of life	EQ-5D [24]	Patient	•	•	•	•	•
Quality of life	WHO-5 Well Being Index (WHO-5) [27]	Patient	•				•
Cognitive functions	Mini Mental State Exam (MMSE) [28]	Physician	•				•
ADL	Barthel Index [29]	Physician	•				•
IADL	Instrumental Activities of Daily Living Scale (IADL) [30]	Physician	•				•
Functioning	Health Assessment Questionnaire (HAQ-DI) [31]	Patient	•				•
Functioning	Hand grip strength measurement [32]	Physician	•				•
Mobility	Timed up and go (TUG) [33]	Physician	•				•
Nutrition	Seniors in the Community Risk Evaluation for Eating and Nutrition (SCREEN II, Version II) [34]	Patient	•				•
Social Support	Fragebogen zur sozialen Unterstützung (F-sozU) [35]	Patient	•				•
Depression	Geriatric depression scale (GDS) [36]	Patient	•				•
Resource use	Questionnaire	Patient	•	•	•	•	•

Twelve months after the index hospitalization all patients who are still alive are invited for a final assessment in the hospital or, if necessary, at home. This examination includes a personal interview with an assessment of functional capacity, mental status and quality of life, adherence to medication, health care utilization, and the measurement of blood pressure and body weight. The study physician and nurse who are involved in the final assessment are not aware whether the respective patient was assigned to the intervention- or control group.

Data on resource utilization as well as on quality of life are collected at baseline, at interim telephone contacts, and during the final assessment.

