### Analysis

The statistical analysis for the primary endpoint will focus on the null hypothesis that there is no difference between intervention and control with respect to the distribution of time to un-planned readmission (including out-of-hospital death). This hypothesis will be statistically tested using a Cox proportional hazards model including age, gender, and comorbidity as covariates.

Statistical analyses for secondary outcomes will be based on (generalized) linear models depending on the type and distribution of the outcome variable. Since these will be multiple tests for which control of the overall error level cannot be achieved, these will be regarded as exploratory analyses. All analyses will be done according to the intent-to-treat approach.

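### The primary endpoint leaves out deaths within 24 hours of an unplanned admission and deaths during a planned stay, and its definition differs between sections

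*Protocol article*

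**What the plan says.** The operational definition is in Baseline and outcome assessments. The clock runs from index discharge to "first unplanned readmission to hospital (at least for 24 hours). Out of hospital death from any cause is counted as an event". The Analysis section keeps the same two limits when it states the null hypothesis for "time to un-planned readmission (including out-of-hospital death", which is to be "statistically tested using a Cox proportional hazards model including age, gender, and comorbidity as covariates". It gives no rule for deaths that meet neither component.

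The Abstract words the endpoint differently, as "time to first readmission to hospital or out of hospital death", with no condition on the type or length of the stay. Objective of the study is equally loose, and Sample size describes the event rate as readmission or out-of-hospital death. No section counts an in-hospital death in its own right.

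On rehabilitation, Home visits and telephone calls postpones the first visit "If the patient stays in a rehabilitation hospital immediately after discharge from the Augsburg hospital". Such a stay therefore falls inside the time at risk. Table 2 lists rehabilitation apart from inpatient care, and no section says whether a rehabilitation facility is a hospital for the endpoint.

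**The concern.** A composite of readmission and out-of-hospital death captures all deaths only when any death in hospital must come after a counted readmission. Here a stay counts only if it is unplanned and lasts at least 24 hours, so some fatal stays are not counted, and the death that ends them is not out of hospital either.

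What is at stake is the meaning of the primary result. A fatal outcome would be an event or not depending on where it happened and how long the patient had been in the building. Death is also not a neutral reason to leave the risk set, because the patient who died cannot be represented by those who remain under observation. The hazard ratio would then refer to a composite with some deaths left out, and it would not translate directly into the event proportions on which the trial is sized.

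**Working it through.** **1. Cases under the operational definition**, for a patient with no earlier qualifying readmission:

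| Death occurs | Qualifying readmission? | Out-of-hospital death? | Event? |
|---|---|---|---|
| At home | No | Yes | Yes |
| After 24 hours or more of an unplanned stay | Yes | No | Yes, at readmission |
| Within 24 hours of an unplanned admission | No (too short) | No | No |
| During a planned stay | No (planned) | No | No |
| In a rehabilitation hospital | Not stated | Depends on whether it is a hospital | Undetermined |

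The third and fourth rows are the gap. Under the looser wording of the Abstract and the Objective, a planned or short stay would itself be an event and the gap would largely close. Those sections therefore conflict with Baseline and outcome assessments and Analysis; they do not share the defect.

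**2. The plan's sample size.** Inputs from Sample size: 40% against 25%, two-sided 5%, 80% power, 10% drop-out. With pooled variance and no continuity correction:

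n = [1.960 × √(2 × 0.325 × 0.675) + 0.842 × √(0.40 × 0.60 + 0.25 × 0.75)]² / 0.15² = 151.9, so 152 per group.

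152 / 0.9 = 168.9, so 169 per group and 338 in total. Both stated figures reproduce.

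**3. How many deaths could be missed.** The document gives no mortality or place-of-death figure, so these inputs are assumptions: one-year mortality 8% to 15%, half of deaths in hospital, and 10% to 30% of those within 24 hours or in a planned or rehabilitation stay.

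- Deaths: 338 × 0.08 = 27 to 338 × 0.15 = 51.
- In hospital: × 0.5 = 13.5 to 25.
- Uncounted: × 0.10 at the low end, × 0.30 at the high end = 1.4 to 7.6.
- Patients with an earlier qualifying readmission already have an event. Removing the planned average event proportion of 32.5%, and assuming independence, gives × 0.675 = 0.9 to 5.1.
- Planned events: 338 × (0.40 + 0.25) / 2 = 109.9. The missed deaths are then 0.9 / 109.9 = 0.8% to 5.1 / 109.9 = 4.7% of that number, or 1.2% to 6.9% before the removal.

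The upper ends include rehabilitation deaths, which may in fact be counted.

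**4. Effect of counting them on the design.** Suppose 1% or 2% of patients (3 or 6 of the 304 evaluable) are added as events.

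| Added | How | n per group for 80% power | Power at 152 per group |
|---|---|---|---|
| 1% | equally in both arms | 155 | 79.4% |
| 2% | equally in both arms | 157 | 78.8% |
| 1% in control | in proportion to arm rates | 147 | 81.5% |
| 2% in control | in proportion to arm rates | 142 | 82.9% |

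The design is hardly affected either way.

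**The case against.** The strongest defence is that this is a condensed article. The intention was probably to capture in-hospital deaths through the readmission that preceded them, and a fuller protocol or analysis plan may state how the rest are handled. It is true that censoring is inferred and not stated. But the article fixes the endpoint explicitly, and applied as written it excludes these deaths. A patient without an event can leave a Cox model only as censored.

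Several stronger readings are tempting and are not supported:

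- **Rehabilitation deaths are lost.** A reader might infer this from the term rehabilitation hospital. If the facility is not a hospital for the endpoint, the death is out of hospital and counts. The document does not settle it, and does not say how many patients go there.
- **Deaths between randomisation and index discharge are censored.** Time starts at discharge, so these patients have no time at risk in this analysis. The window is also short, since baseline is usually taken one or two days before discharge.
- **The gap favours the programme.** One could argue that earlier care-seeking moves deaths from home into the first hours in hospital. If 3 of 169 intervention patients were so moved, the arm difference would shift by 1.8 points of the planned 15 with no life saved. But earlier care-seeking could equally turn home events into counted stays or add counted admissions, which works against the programme. Nothing in the document supports a net direction.
- **The sample size is wrong.** It reproduces exactly and does not depend on this gap.

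**Conclusion.** The concern holds for two kinds of death in patients with no earlier qualifying readmission: within 24 hours of an unplanned admission, and during a planned hospital stay. Two lesser points stand beside it. The handling of rehabilitation deaths is undetermined, and the sections do not agree on which readmissions count.

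The size is probably small, about 1 to 5 patients in the whole trial once earlier events are removed. That range rests entirely on assumed mortality and place-of-death shares and on independence between earlier readmission and type of death. It should be read as an illustration and not as an estimate. The point still deserves correction because it concerns the primary endpoint and the outcome left out is death.

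**What to change.** Before any unblinded analysis, define the primary event as the first unplanned readmission lasting 24 hours or more, or death from any cause wherever it occurs after index discharge, including in any hospital or rehabilitation hospital. Use that wording in the Abstract, Objective of the study, Baseline and outcome assessments, Analysis and Sample size.

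This changes one sentence and aligns four other places. No new data are needed: the final assessment already requires knowing who is alive at twelve months, and the planned cost per life year saved requires survival times. The assumed 40% and 25% may shift slightly, with the negligible effect on power shown above.
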